### Outcome measures

All outcome assessments will be completed within 1 week before the intervention and within 1 week after completion of the 8-week intervention. The testing sequence will remain consistent across participants and time points. The dominant leg (preferred kicking leg) will be used for knee muscle strength testing (Table 5).

**Table 5 tab5:** Outcome measures, assessment tools and interpretation criteria.

Outcome category	Measure	Instrument	Interpretation
Primary outcome	Knee extensor peak torque (EPT)	Multi-joint isokinetic strength testing and training system, Model A8-2, at 60 degrees/s	Higher value indicates greater knee extensor strength.
Primary outcome	Knee flexor peak torque (FPT)	Multi-joint isokinetic strength testing and training system, Model A8-2, at 60 degrees/s	Higher value indicates greater knee flexor strength.
Primary outcome	Hamstring-to-quadriceps ratio (H/Q)	Calculated from flexor and extensor peak torque	Higher balanced ratio indicates improved flexor-extensor strength balance.
Secondary outcome	Overall Stability Index (SI)	Biodex Balance System, bipedal dynamic balance test	Lower value indicates better balance capacity.
Secondary outcome	Anteroposterior Stability Index (APSI)	Biodex Balance System, bipedal dynamic balance test	Lower value indicates better anterior–posterior stability.
Secondary outcome	Mediolateral Stability Index (MLSI)	Biodex Balance System, bipedal dynamic balance test	Lower value indicates better medial-lateral stability.
Safety outcome	Adverse events and exercise-related discomfort	Instructor record form and participant report	Events summarized by type, severity, relation to intervention, and outcome.

### Knee muscle strength testing

A multi-joint isokinetic strength testing and training system will be used to assess knee muscle strength. Isokinetic testing is the gold standard for evaluating maximal knee strength, and testing at an angular velocity of 60°/s is the most efficient and reliable approach for measuring maximal muscle strength (26). Therefore, peak torque of the knee extensors and flexors, as well as the H/Q ratio, will be measured at 60°/s. An H/Q ratio ≥ 0.60 is considered desirable, whereas a ratio < 0.55 indicates relative hamstring weakness and an increased risk of non-contact knee injury. An increase in the H/Q ratio after the intervention will be interpreted as improved muscle balance (27). Before formal testing, each participant will complete 3–5 submaximal knee flexion-extension repetitions as a warm-up. Under the supervision of a qualified therapist and within a pain-free range of motion, the participant will then perform five maximal-effort knee flexion and extension repetitions to ensure accurate data collection (28). The dominant leg (preferred kicking leg, cross-verified by a functional task such as stepping onto a curb (29)) will be tested. Testing only the dominant leg avoids confounding from baseline strength differences between legs.

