## Objectives and hypotheses

The primary objective is to evaluate the effects of an 8-week Tai Chi Chuan combined with unstable resistance training programme on knee flexor and extensor strength in female college students, compared with Tai Chi Chuan alone and unstable resistance training alone.

The secondary objective is to compare the effects of the three intervention modalities on dynamic balance capacity under eyes-open and eyes-closed conditions.

The main hypothesis is that the combined intervention will produce greater improvements in knee flexor peak torque, knee extensor peak torque, H/Q ratio, and dynamic balance indices than either single-modality intervention. A secondary hypothesis is that Tai Chi Chuan alone will show particular advantages in proprioception-dependent balance and H/Q optimization, while unstable resistance training alone will show particular advantages in rapid improvement of extensor strength.

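### Any rise in H/Q is to be read as improved muscle balance, whatever drives it and wherever it starts, and no joint reading with the two torques is required

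*Protocol article*

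**What the plan says.** Table 5 (Outcome measures) lists three primary outcomes: knee extensor peak torque, knee flexor peak torque and H/Q. H/Q is "Calculated from flexor and extensor peak torque", and its interpretation is "Higher balanced ratio indicates improved flexor-extensor strength balance"; the qualifier on the ratio is not defined. For extensor torque the table says "Higher value indicates greater knee extensor strength", and flexor torque is read in the same direction.

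Knee muscle strength testing gives two reference values: "An H/Q ratio ≥ 0.60 is considered desirable, whereas a ratio < 0.55 indicates relative hamstring weakness". The next sentence sets the reading rule without reference to them: "An increase in the H/Q ratio after the intervention will be interpreted as improved muscle balance".

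Objectives and hypotheses expects that "the combined intervention will produce greater improvements in knee flexor peak torque, knee extensor peak torque, H/Q ratio, and dynamic balance indices" compared with either single modality. It also expects that "unstable resistance training alone will show particular advantages in rapid improvement of extensor strength". The Introduction adds that training built on squats, lunges and heel raises may favour the extensors.

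Statistical analysis tests each primary outcome between groups by one-way ANOVA (or Kruskal-Wallis) at 0.05/3, names no baseline covariate, and plans within-group pre-post tests. It does not say how an H/Q result is to be read against its two components.

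**The concern.** A ratio has two ways to rise, and only one of them involves a stronger hamstring. The rule treats both alike. It also treats a rise from a value already in the desirable range like a rise out of the range that "indicates relative hamstring weakness and an increased risk of non-contact knee injury".

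This matters here because numerator and denominator are both primary outcomes for which higher is better, and the protocol expects one arm to gain mainly in the denominator. Unless flexors gain proportionally as much, that gain lowers the arm's H/Q. Another arm can then look better on H/Q because its extensors gained proportionally less. Since H/Q has its own significance threshold, such a result could be reported as a benefit on a primary outcome without any advantage in strength behind it. The planned within-group tests invite the same reading directly, because the rule is phrased as an increase after the intervention.

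**Working it through.** **Inputs from the protocol.** H/Q = flexor peak torque / extensor peak torque (Table 5). Marks 0.55 and 0.60 (Knee muscle strength testing). Significance threshold per primary outcome 0.05/3 = 0.0167, which agrees with the stated 0.017 (Statistical analysis).

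**Inputs assumed.** The protocol gives no baseline torque, baseline H/Q or expected percentage change, so all torque values and changes below are illustrations.

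**Identity.** With f and e the proportional changes in flexor and extensor torque:

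H/Q after = H/Q before × (1 + f) / (1 + e)

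H/Q therefore rises exactly when f > e, whatever the signs of f and e.

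**Cases within one participant or arm.**

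| Before | f | e | Calculation | After | Reading under the rule |
|---|---|---|---|---|---|
| 0.55 | 0 | −10% | 55/90 | 0.611 | improved, past 0.60; extensor weaker, flexor unchanged |
| 0.54 | 0 | −10% | 0.54/0.90 | 0.600 | improved, from below 0.55 to the desirable mark; no flexor gain |
| 0.60 | −5% | −15% | 0.60 × 0.95/0.85 | 0.671 | improved; both muscles weaker |
| 0.65 | 0 | −10% | 0.65/0.90 | 0.722 | improved; already above 0.60 |
| 0.60 | +10% | 0 | 0.60 × 1.10 | 0.660 | improved; flexor stronger, extensor maintained |

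The rule gives the first four rows the same label as the last.

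**Case between arms.** Suppose both arms start at 0.60 and both gain 10% in flexor torque. Arm A gains 5% in extensor torque and arm B gains 20%.

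- Arm A: 0.60 × 1.10/1.05 = 0.629
- Arm B: 0.60 × 1.10/1.20 = 0.550
- Ratio of the two: 0.629/0.550 = 1.14, which equals 1.20/1.05

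The flexor contrast is nil. The whole between-arm H/Q difference comes from arm A's smaller extensor gain.

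**Why logs separate the parts.** log(H/Q) = log(flexor) − log(extensor). Least squares is linear in the outcome. If the three log outcomes are fitted with the same covariates to the same participants, the group effect on log(H/Q) equals the group effect on log flexor minus that on log extensor. In the first row the log changes are 0 for flexor and ln(0.90) = −0.105 for extensor, so log(H/Q) changes by 0 − (−0.105) = +0.105, and exp(0.105) = 1.11 = 0.611/0.55. If each model adjusts only for its own baseline, the covariates differ and the equality no longer holds exactly.

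**The case against.** The strongest reply is that the sentence speaks of balance, not strength. A move from 0.55 to 0.61 does go towards the protocol's own desirable range, and strength is answered by other outcomes. Both torques are primary, so an H/Q rise caused by extensor loss would show in the extensor result. The main hypothesis names flexor torque, extensor torque, H/Q and the balance indices together, so H/Q alone would not establish it. Nor does the protocol expect extensor torque to fall over 8 weeks of supervised training.

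All of this stands, and it limits the harm. It does not remove the gap: the components are measured, but nothing requires them to be read with the ratio, the separate threshold permits a claim on H/Q alone, and the rule ignores the marks given one sentence before it.

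A reader might also infer that the plan penalises strength gains. With a 10% flexor and a 20% extensor gain from 0.58, H/Q falls to 0.58 × 1.10/1.20 = 0.532, below 0.55, although both muscles are stronger. The documents do not support that inference. They never say that a fall in H/Q is harm. The 0.55 mark denotes relative weakness, and the hamstrings in this example have become relatively weaker. The split between arms on H/Q and extensor strength is itself one of the stated hypotheses.

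**Conclusion.** The point holds as a defect in a stated reading rule. Any H/Q increase is to be called improved balance, unconditionally, for a primary outcome with its own threshold of 0.017. The algebra is certain. How often it would matter cannot be sized, because the protocol gives no torque or H/Q values; the move from 0.55 to 0.61 rests on assumed torques and an assumed 10% extensor loss.

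It would go too far to say that H/Q rises merely because extensors gain less. The extensor gain must be proportionally smaller than the flexor gain, and then a rise from a low baseline can be a real improvement in balance. It would also go too far to say that an extensor loss would go unseen, since the extensor outcome would show it. What is missing is a commitment, made before results are known, to read the three together. The sample size calculation is not affected.

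**What to change.** Replace the reading rule in Knee muscle strength testing, and align the Table 5 entry, along these lines: a between-group difference in H/Q will be interpreted only together with the flexor and extensor torque contrasts (estimates with confidence intervals) and the 0.55 and 0.60 marks, and will not be claimed alone as a benefit when it is explained by lower extensor torque.

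In Statistical analysis, analyse log(H/Q), log flexor torque and log extensor torque by ANCOVA. Use the same covariates in all three models: baseline log flexor and baseline log extensor torque. The H/Q effect then equals the flexor effect minus the extensor effect exactly within each dataset, including each imputed one provided H/Q is calculated from the imputed torques and not imputed separately. Adjusting for baseline should also improve precision over unadjusted ANOVA, to the extent that baseline predicts the final value.

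Report the proportions below 0.55 and at or above 0.60 by arm as description only; at 19 per arm they are too imprecise to test.

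The cost is one replaced sentence and a changed model. No new measurements or participants are needed. The downsides are that H/Q can no longer be claimed as a win by itself, and that effects are reported as ratios rather than in Nm or ratio points. The change should be made before any results by arm are seen.

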**Methods:**

This protocol describes a single-center, parallel-group, randomized controlled trial. Fifty-seven healthy female college students aged 18–22 years will be recruited from Fenyang College, Shanxi Medical University, and randomly allocated in a 1:1:1 ratio to a Tai Chi Chuan group (TCC), unstable resistance training group (URT), or Tai Chi Chuan combined with unstable resistance training group (T + URT). All interventions will last 8 weeks, with three 60-min sessions per week. The primary outcomes will be dominant-leg knee extensor peak torque, knee flexor peak torque, and hamstring-to-quadriceps ratio measured using an isokinetic strength testing system at 60 degrees/s. Secondary outcomes will include overall stability index, anteroposterior stability index, and mediolateral stability index under eyes-open and eyes-closed conditions measured with the Biodex Balance System. Assessments will be conducted at baseline and after the 8-week intervention. Intention-to-treat and per-protocol analyses will be used. Missing data will be handled using multiple imputation where appropriate.

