### Dynamic balance testing

Dynamic balance will be evaluated using the Biodex Balance System. This device has established good-to-excellent intratester reliability for stability indices in healthy university students (ICC = 0.85 for SI, 0.78 for APSI, and 0.84 for MLSI during static stance) and has been widely validated for dynamic balance assessment (30). Participants will stand barefoot on the platform at stability level 8, with fixed heel coordinates and toes abducted at approximately 30 degrees. During the eyes-open test, participants will focus on the screen and attempt to keep the cursor centered for 20 s. During the eyes-closed test, the same posture and task duration will be used without visual input. Each condition will be repeated three times, and the mean value will be used for analysis. SI, APSI, and MLSI will be extracted. Lower index values indicate better balance capacity (31).

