### Statistical analysis

Two analysis sets will be used. The intention-to-treat set will include all randomized participants in their originally allocated groups regardless of adherence or withdrawal. The per-protocol set will include participants who complete the full intervention protocol without major protocol deviations. The primary analysis will be based on the intention-to-treat principle, and the per-protocol analysis will be used as a sensitivity analysis.

Missing data will be handled using multiple imputation when the missingness mechanism is considered missing at random. Baseline knee muscle strength, dynamic balance index values, age, height, and weight will be considered predictor variables for imputation. Five imputed datasets will be generated using a multiple linear regression model in SPSS 25.0. Pooled estimates will be calculated according to Rubin’s rules. If missing data are minimal, complete-case analysis may be reported as a supplementary analysis.

Categorical variables will be expressed as n (%). Normally distributed quantitative variables will be presented as mean ± standard deviation, and non-normal data as median (interquartile range). Normality will be tested with the Shapiro–Wilk test, and variance homogeneity with Levene’s test. For within-group pre–post comparisons, paired t-tests will be used for normally distributed data; otherwise, Wilcoxon signed-rank tests will be applied. Between-group differences will be assessed using one-way ANOVA for parametric data, followed by Bonferroni-adjusted pairwise comparisons when the overall effect is significant. Non-parametric data will be analyzed with the Kruskal–Wallis test, followed by Dunn–Bonferroni pairwise comparisons. Categorical variables will be compared using the chi-square test or Fisher’s exact test. Given three primary outcomes (knee extensor peak torque, knee flexor peak torque, and hamstring-to-quadriceps ratio), a Bonferroni correction will be applied to control multiplicity, with a significance threshold set at *p* < 0.017 (0.05/3). Secondary outcomes are exploratory, a two-sided *p* < 0.05 will be used without multiplicity correction.

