## Discussion

This study protocol proposes a rigorous randomized controlled trial to evaluate whether Tai Chi Chuan combined with unstable resistance training can improve knee muscle strength and dynamic balance in female college students. The study responds to a practical need: many college students have insufficient physical activity, while female students may be at increased risk of lower-limb injury during sport and daily physical activity (7, 33, 34). An efficient, safe, and feasible training model may therefore have value for university health promotion.

The combined intervention is designed around a central-peripheral rationale. Tai Chi Chuan emphasizes movement awareness, controlled weight shifting, breathing coordination, and continuous adjustments of the body center of mass. These characteristics may support central sensory integration and proprioceptive control (35–37). Unstable resistance training, by contrast, provides stronger peripheral loading to the knee musculature and challenges stabilizing muscles through unstable surfaces (38, 39). The combination is expected to improve both the neural control and muscular execution components of lower-limb function.

Compared with Tai Chi Chuan alone, the combined programme may overcome the limitation of slower strength improvement by adding targeted resistance stimulation. Compared with unstable resistance training alone, it may compensate for the limitation of extensor-dominant loading by improving flexor-extensor coordination and proprioceptive regulation. Therefore, the combined intervention may produce broader functional benefits than either single intervention (40, 41).

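### Pre-post significance tests within three active arms cannot show that a programme works; report within-arm change as description only (minor)

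*Protocol article*

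**What the plan says.** Study design and setting allocates participants to Tai Chi Chuan, unstable resistance training or the combination; no arm is untrained. The abstract fixes two test occasions: "Assessments will be conducted at baseline and after the 8-week intervention".

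Statistical analysis plans two kinds of comparison. Within arms: "For within-group pre–post comparisons, paired t-tests will be used for normally distributed data; otherwise, Wilcoxon signed-rank tests will be applied". Between arms: "Between-group differences will be assessed using one-way ANOVA for parametric data, followed by Bonferroni-adjusted pairwise comparisons when the overall effect is significant". The within-arm tests are not labelled descriptive, and nothing says what may be concluded from them.

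Knee muscle strength testing describes the sequence at a visit: "each participant will complete 3–5 submaximal knee flexion-extension repetitions as a warm-up", after which "the participant will then perform five maximal-effort knee flexion and extension repetitions to ensure accurate data collection". The same section says that a post-intervention rise in H/Q, one of the three primary outcomes, is to be taken as better muscle balance. It does not tie that reading to a difference between arms. For the Biodex indices, Dynamic balance testing says: "Each condition will be repeated three times, and the mean value will be used for analysis".

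Objectives and hypotheses is comparative throughout: the combination against each single programme. The Discussion opens with a different question, namely "whether Tai Chi Chuan combined with unstable resistance training can improve knee muscle strength and dynamic balance in female college students".

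**The concern.** A pre-post difference in one arm is the sum of any training effect and everything else that differs between the two visits. Peak torque depends on maximal voluntary effort, and the eyes-open balance test depends on learning to hold a cursor centred, so some gain on second exposure is plausible. Time may add to it, as may regression to the mean, although the eligibility criteria select on recent inactivity and not on low strength or balance. An untrained arm would show how large these components are; this design has none.

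A paired test asks only whether the total change differs from zero, so it can be significant when training did nothing. What is at stake is a statement that a programme improves strength or balance, supported by a within-arm p-value. The H/Q sentence and the Discussion's opening question both invite such a statement.

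**Working it through.** **Passages side by side.** The within-arm tests ask whether each arm changed. The H/Q sentence reads such a change as benefit. The Discussion's opening question is of the same kind. Objectives and hypotheses asks whether the combination changes more than each single programme. Only that last question can be answered with three active arms.

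**Inputs from the protocol.** The protocol gives no figure for the within-arm tests, so there is none to reproduce. The Sample size section gives 16 evaluable participants per arm and about 15% dropout: 16 / 0.85 = 18.8, hence the stated 19 enrolled per arm. The within-arm illustration uses both numbers. Statistical analysis sets a threshold of 0.017 (0.05/3) for primary outcomes and does not say whether it also applies to the paired tests, so both 0.05 and 0.05/3 are shown where they matter.

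**Assumptions, none of them in the protocol.** Zero training effect; practice gain in peak torque of 5% of the baseline mean, with 1% and 2% as smaller cases; between-person CV 15–20%; equal variances at both visits; pre-post correlation r = 0.8, with 0.5 as an alternative.

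**Formula.** The standardised mean change is dz = (gain / CV) / √(2(1 − r)). The rejection probability of the two-sided paired t-test comes from the noncentral t distribution with n − 1 degrees of freedom and noncentrality dz·√n.

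**Worked case, 5% gain, r = 0.8, n = 19.** √(2 × 0.2) = 0.632.
- CV 15%: dz = 0.333 / 0.632 = 0.527; noncentrality 0.527 × √19 = 2.30; rejection 0.585.
- CV 20%: dz = 0.250 / 0.632 = 0.395; noncentrality 1.72; rejection 0.371.

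**Results for one arm at 0.05** (5% would be nominal):

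| Gain | n | r | CV 20% | CV 15% |
|---|---|---|---|---|
| 5% | 19 | 0.8 | 37% | 59% |
| 5% | 16 | 0.8 | 32% | 51% |
| 5% | 19 | 0.5 | 18% | 28% |
| 2% | 19 | 0.8 | 10% | 14% |
| 1% | 19 | 0.8 | 6% | 7% |

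At 0.05/3 the first row becomes 21% and 39%, against a nominal 1.7%.

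**Between-arm check.** In 20,000 simulated trials with 19 per arm, r = 0.9, no training effect and the same shift of 0.3 SD in every arm, the ANOVA at 0.05/3 rejected in about 1.7% of runs. That held for post-test values and for change scores. This is the nominal level.

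**Limits.** The calculation concerns peak torque. An equal proportional gain in flexors and extensors would leave H/Q unchanged, and nothing was computed for the balance indices.

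**The case against.** The strongest defence is that the trial's inference lies elsewhere. The main hypothesis is comparative, the sample size is set for a three-group ANOVA, and the pairwise comparisons are Bonferroni-adjusted. A practice shift common to randomised arms cancels there, as the simulation confirms. The opening sentence of the Discussion is introductory, and the paragraphs after it return to comparisons with each single programme. The H/Q sentence may be meant only to give the direction of the scale. All of this stands, and it is why the point is minor. It does not remove the within-arm tests, which are stated and unrestricted.

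The size is also open to challenge. Gain, CV and correlation are all assumed, and with a 1% gain the excess over 5% is negligible. Whether one earlier test still helps 8 weeks later is not in the protocol. That stands too: the table is an illustration, not an estimate.

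A reader might go further and infer that participants have never used either device, that they receive no familiarisation, and that the primary comparison is therefore biased. The document does not support this. Eligibility requires no regular exercise in the previous 3 months and is silent on prior use of the equipment. Quality control and data monitoring refers to a written assessor procedure that is not shown, so the absence of unscored practice cannot be established from a condensed article. Nor can one say that an unpractised first balance trial adds noise to a baseline used in every comparison: the ANOVA is not stated to use baseline, and the sample size rests on post-intervention torque.

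**Conclusion.** The point holds in a limited form and is minor. Three active arms with one test before and one after cannot attribute a within-arm change to training, yet the plan tests such changes for significance and reads a rise in one primary outcome as improvement. That conclusion follows from the stated design and needs no assumption about practice effects. Only the size does: across the cases tabulated, the false-positive rate of a one-arm paired test at 0.05 runs from about 6% to 59%, depending mainly on the assumed practice gain. The between-arm comparison that carries the objectives is not biased by a shift common to all arms.

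**What to change.** 1. In Statistical analysis, report within-arm change as an estimate with a confidence interval, label it descriptive, drop the significance claim, and state that all efficacy conclusions rest on between-arm contrasts.
2. In Knee muscle strength testing, tie the reading of a higher H/Q ratio to a difference between arms.
3. In the opening of the Discussion, replace the improvement question with the comparative one in Objectives and hypotheses: whether the combination improves outcomes more than either single programme.

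These three changes cost wording only.

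Optional: state whether unscored practice precedes scoring. If the assessor procedure does not already include it, add a brief one on each device, identical at both visits. This costs a few minutes per visit and has to be settled before baseline testing, which the Participant timeline section places from May 2026. It may not remove learning carried from the first visit to the second, so it does not replace change 1.
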